#### Observer ratings of movement execution (phase 2).

The participants’ performance of movement execution for the six movement tasks will be rated by a trained observer in both conditions as described in Additional file 1. The scale ranges from 0 to 3 with lower ratings showing a better performance.

#### Stress (phase 2).

Task-related stress is assessed via self-report before and after each set of movement tasks. For this purpose the SSSQ-G [60] will be used, a 24-item questionnaire answered on a 5-point Likert scale (1 = *not*
*at*
*all*; 5 = *extremely*). As a pre- and a post-version exist, the questionnaire allows for evaluation of changes in acute task-related stress. The SSSQ-G assesses six facets of subjective task-related stress: Distress, Worry, Confidence, Negative Affect, Motivation, and Self-evaluation. Higher scores indicate a higher subjective level of stress.

Psychophysiological stress markers include unstimulated saliva samples (Salivette®, Sarstedt, Nümbrecht, Germany) to measure salivary cortisol and alpha-amylase levels indicating HPA axis and sympathetic nervous system (re-)activity, respectively. Salivary samples will be collected at four timepoints: baseline (s0), before the first set of movements tasks (s1), directly after the two sets of movements tasks (s2), and 15 min after s2 (s3). Saliva samples will be analyzed in the laboratory of the Chair of Health Psychology at Friedrich-Alexander-Universität Erlangen-Nürnberg (Nürnberg, Germany). After the collection, samples will be stored at −20°C for a maximum duration of 12 months. If longer storage times will be necessary, samples will be stored at −80°C. A maximum of two freeze-thaw cycles will be permitted. Prior to analyzing cortisol and alpha-amylase concentrations, samples will be thawed and centrifuged at 2000g for 10 min. To determine cortisol concentrations Cortisol Saliva Luminescence Immunoassays (CLIA, IBL, Germany) and for alpha-amylase concentrations kinetic/ colorimetric enzymatic assays will be used. To account for influences of menstrual cycle hormones, progesterone and estradiol concentrations derived from unstimulated passive drool samples will be analyzed using either high-sensitive Enzyme-linked Immunosorbent Assays (ELISA) or Liquid Chromatography-mass Spectrometry (LC-MS), depending on expected concentration ranges and availability of sensitive assay kits.

We will further record a 1-channel electrocardiogram (ECG) with a wearable ECG sensor (Portabiles GmbH, Erlangen, Germany; Lead I according to Einthoven’s Triangle) during the movement tasks. From the ECG, we will extract heart rate (HR) and established heart rate variability (HRV) metrics as markers for autonomic (re)activity [75].

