Phase 2 will examine differences between participants with and without experimentally induced lower back pain in back-pain-related movement parameters during standardized movement tasks and investigate the related stress responses. In addition, we will collect self-report data on FA and investigate whether FA moderates the movement parameters and stress responses in the pain condition.

The following hypotheses will be tested:

(1) The task-related ratings of pain intensity are higher in the condition with the back pain simulator (PainSim+) than without (PainSim-).(2) The fear of movement ratings are higher in the condition with the low back pain simulator (PainSim+) than without (PainSim-).(3a) The task-related ratings of motion impairment are higher in the condition with the back pain simulator (PainSim+) than without (PainSim-).(3b) The mobility (measured through lumbar range of motion (LROM), lumbar flexion (LF), and movement velocity (MV)) is lower in the condition with the low back pain simulator (PainSim+) than without (PainSim-).(3c) Observer ratings of performance of task execution are worse in the condition with the low back pain simulator (PainSim+) than without (PainSim-).(4a) The task-related ratings of emotional distress are higher in the condition with the low back pain simulator (PainSim+) than without (PainSim-).(4b) The subjective stress ratings is higher in the condition with the low back pain simulator (PainSim+) than without (PainSim-).(4c) The heart rate variability (HRV) is lower in the condition with the low back pain simulator (PainSim+) than without (PainSim-).

In exploratory analyses, we will examine whether even in this analogue sample self-reported FA is associated negatively with mobility and HRV, and positively with subjective stress reports, salivary stress markers (alpha-amylase, cortisol), and pain ratings.

This integrated design allows for the combined assessment of physiological stress responses, behavioral changes, and movement-related aspects across standardized back-stressing movements.

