### Lab appointment

Prior to the lab appointment participants will be informed via e-mail about the following instructions and restrictions: Waking up at least three hours before the appointment, no eating and caffein consumption one hour before the appointment, no smoking or exercise two hours before the appointment, and wearing comfortable clothes with thin fabric (no dresses or skirts). The lab appointment begins with the experimenters obtaining written informed consent. Participants then provide a baseline saliva sample for stress assessment (s0), which includes carefully moving a cotton roll (Salivette®, Sarstedt, Nümbrecht, Germany) in their mouth for 1.5 min. Afterwards, their body weight, height, and waist and hip circumference are measured. Female participants additionally provide a saliva sample of 5 ml via passive drooling (pooling saliva in the mouth and allowing it to drip into the sample tube) for the analysis of progesterone and estradiol levels as they might influence pain perception [57,58] and stress responses [35,59]. The core part of the experiment is conducted under two conditions in randomized order, namely, once with and once without the back pain simulator to allow for within-subject comparison. Before each condition, participants complete the Short Stress State questionnaire (SSSQ-G; [60]) and provide another saliva sample (s1). Participants then perform six movement tasks: five from the Back Performance Scale [61] and a sit-to-stand task (comparable to [62]; adjusted arm position: hands are placed relaxed on the legs). Movement quality is rated by an experimenter (see Additional File 1), and a video of the movement execution is recorded. Throughout the tasks, participants wear an inertial measurement unit (IMU)-based motion capture suit (Xsens MVN, Movella, Henderson USA; for more details see [63]). In phase 2, this will be supplemented by the EmpkinS holographic 6D wireless locating technique and integrated localizable electromyography radio transponders (EmpkinS sensor technology; [64,65]). After each task, participants rate pain intensity, emotional distress, and pain-related impairment on a visual analogue scale (VAS). Following task completion, the SSSQ-G and a third saliva sample (s2) are collected. The entire procedure is repeated under the alternate condition (with/ without low back pain simulator), including an SSSQ-G assessment before and after the six movement tasks, as well as another saliva sample (s3) after the movement tasks. In total, each participant completes 2x6 movement tasks, provides 4 saliva samples, and 2x2 SSSQ-G assessments.

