### Statistical methods

Qualitative analysis on feasibility and acceptability in phase 1 will be carried out with MAXQDA Analytics Pro [80]. Data of phase 2 will be analyzed using a repeated-measures design. Correlations of dependent variables will determine if multivariate analyses of variance (MANOVAs) or separate analyses of variance (ANOVAs) are indicated, following common recommendations of moderate intercorrelation [81].

The first MANOVA will include the within-subjects factor *condition* (PainSim + vs. PainSim-) and dependent variables measuring task-related fear of movement, pain intensity, impairment and emotional distress. A second MANOVA will assess *mobility* (LROM, LF, MV). And a third MANOVA will examine stress (HRV, salivary cortisol, salivary amylase, subjective stress) in the same manner. Psychophysiological data (e.g., HRV-data) that deviate (significantly) from the other data (i.e., outliers) will be excluded in accordance with the established practices in the literature. The pattern of missing data is tested with MCAR-test. If the missing data is missing completely at random, we will conduct multiple imputation.

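### The two saliva schedules conflict, and under the one in the Stress outcome section the planned condition contrast for cortisol and amylase cannot be estimated

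*Protocol article*

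**What the plan says.** **Lab appointment.** The session opens with "Participants then provide a baseline saliva sample for stress assessment (s0". Next comes "Before each condition, participants complete the Short Stress State questionnaire (SSSQ-G; [60]) and provide another saliva sample (s1". After the first block, "Following task completion, the SSSQ-G and a third saliva sample (s2) are collected". The procedure is then repeated in the other condition, "as well as another saliva sample (s3) after the movement tasks". The section's own tally is that "each participant completes 2x6 movement tasks, provides 4 saliva samples, and 2x2 SSSQ-G assessments".

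**Outcomes, Stress (phase 2).** This section also counts four saliva timepoints and uses the same labels, but after the baseline it places them "before the first set of movements tasks (s1), directly after the two sets of movements tasks (s2), and 15 min after s2 (s3".

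**Statistical methods.** The first MANOVA has the within-subject factor condition (PainSim+ against PainSim-). "And a third MANOVA will examine stress (HRV, salivary cortisol, salivary amylase, subjective stress) in the same manner".

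**Introduction.** Hypotheses 4a to 4c concern emotional distress, subjective stress and HRV. The salivary markers appear only in the exploratory fear-avoidance analyses, where fear avoidance is expected to be associated "positively with subjective stress reports, salivary stress markers (alpha-amylase, cortisol), and pain ratings".

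**The concern.** A within-subject condition effect needs, for each participant, at least one value that belongs to PainSim+ and one that belongs to PainSim-. The two sections give s2 and s3 different meanings under the same labels, and only one of those meanings supplies such values for saliva.

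The timing of a sample cannot be repaired after the session. If experimenters follow the outcome section, the condition contrast for cortisol and amylase is lost for good. The shared labels also make the error easy to miss: an analyst who follows the Lab appointment section could assign s2 to the first condition and s3 to the second. If the samples were in fact taken at the end of the session and 15 minutes later, the software would still return a result, but it would describe recovery time and not condition.

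**Working it through.** **1. The two schedules side by side**

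| Sample | Lab appointment | Stress (phase 2) |
|---|---|---|
| s0 | baseline, before both conditions | baseline, before both conditions |
| s1 | before each condition | before the first set |
| s2 | after the first condition | after both sets |
| s3 | after the second condition | 15 min after s2 |
| Stated total | 4 | 4 |
| Post-task samples belonging to one condition | 1 per condition | 0 |

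**2. Count check, Lab appointment.** Taken literally, s0 (1) + s1 (2) + s2 (1) + s3 (1) = 5, against the stated 4. Four is reached only if s1 is taken once and s2 doubles as the pre-sample of the second condition.

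**3. Estimability.** Model each marker with 56 participant effects, 3 time effects (s1, s2 and s3 against s0) and 1 condition effect: 56 + 3 + 1 = 60 columns.

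- *Lab appointment schedule:* the condition code is +1 or -1 at s2 and the reverse at s3, with the sign set by the randomized order. The rank is 60 of 60, so the condition effect is estimable.
- *Outcome-section schedule:* s0 and s1 precede both conditions, and s2 and s3 follow both. No sample carries a condition code and the rank is 59 of 60. Coding each sample by the exposures completed so far does not help. The PainSim+ and PainSim- columns are both 0 at s0 and s1 and both 1 at s2 and s3, so each equals the sum of the s2 and s3 time columns. The rank is then 59 of 61.

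**4. What the Lab appointment schedule estimates.** Let τ+ and τ- be the condition effects, π2 and π3 the time effects at s2 and s3, and λ+ and λ- any carryover of the first condition into s3. The expected value of s2 - s3 is:

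- PainSim+ first: (τ+ - τ-) + (π2 - π3) - λ+
- PainSim- first: -(τ+ - τ-) + (π2 - π3) - λ-

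Half the difference between the two orders is (τ+ - τ-) - (λ+ - λ-)/2. The time effect cancels. The contrast is unbiased if carryover is the same after both conditions, and otherwise off by half the difference in carryover. The document gives no interval between the sets, so this cannot be sized.

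**5. What remains under the outcome-section schedule.** Only a comparison between order groups at s2 and s3 is left, that is, which condition came last.

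- The plan's sample size is reproduced first. A two-sided paired t-test with d = .40 and alpha = .05 has power 0.7999 at N = 51, which rounds to the stated .80 (a strict 0.80 needs 52). Adding 10%: 51 × 1.10 = 56.1, stated as 56.
- With 56 participants and equal orders, the comparison is 28 against 28. For a standardized difference of 0.40 its power is about 0.32, against 0.84 for a paired contrast with d = 0.40 at N = 56. The two standardized differences are on different scales (between persons and within person), so this only illustrates the loss. It is also a different question from the planned one.

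**6. The other two outcomes of the third MANOVA.** The outcome section records the ECG during the movement tasks and gives the SSSQ-G before and after each set. Both therefore have a PainSim+ and a PainSim- value under either saliva schedule.

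**The case against.** **The outcome section may mean after each set.** That reading gives two s2 samples and five in all, against the stated four, and leaves it unclear which s2 starts the 15 minutes to s3. It does not rescue the text.

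**The timeline figure (S2 Fig) may settle the matter.** It is not at hand and may well show the schedule in use. It can agree with at most one of the two sections, so the conflict in the text remains. What follows is that the text conflicts, not that the data will certainly lack a condition contrast. This stands.

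**A reader might infer that the defect takes hypotheses 4b and 4c down with it.** The document does not support that. HRV and the SSSQ-G are measured per condition whatever the saliva timing, and Statistical methods allows separate ANOVAs in place of a MANOVA, depending on how the dependent variables correlate. What fails under the outcome-section schedule is the four-outcome joint test, and equally any ANOVA of saliva by condition.

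**A reader might also infer that saliva is uninterpretable under either schedule.** That goes too far. Under the Lab appointment schedule the contrast has full rank and the order is randomized. Carryover into s3 is a risk of unknown size, and the missing fresh pre-sample for the second condition is a limitation of the design rather than an error. Taking saliva out of the MANOVA is therefore needed only if s2 and s3 both follow both conditions.

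**No numbered hypothesis uses saliva.** This is true, and it limits the damage. But the abstract lists salivary cortisol among the stress parameters and expects stress responses to be higher in the pain condition, and Statistical methods tests both markers by condition.

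**Conclusion.** The point holds. The Lab appointment and Stress sections give s2 and s3 incompatible times, and the s1 wording in the Lab appointment section does not fit its own total of four. Under the outcome-section schedule the within-subject condition effect on two of the four dependent variables of the third MANOVA is not estimable, and a larger sample would not change that. Under the Lab appointment schedule it is estimable from one post-task sample per condition, subject to differential carryover.

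The conclusion rests on reading both sections literally, and on the third MANOVA having the same condition factor as the first. It is confined to cortisol and amylase: the data for 4b and 4c and the sample size are unaffected. It should be settled before phase 2 starts, because the sampling times cannot be recovered later.

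**What to change.** Before phase 2, write one four-sample schedule and use it in the Lab appointment section, the Stress outcome section and the experimenter checklist. The procedure is described as the same in both phases apart from small adjustments, so the phase 1 session records should show which schedule has been followed.

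- **If s2 follows the first condition and s3 the second:** correct the Stress outcome section, and reword the Lab appointment section so that s1 is taken once. Analyse the saliva condition contrast with adjustment for period and order. State that s2 is the only pre-sample for the second condition and that carryover into s3 is possible.
- **If s2 and s3 both follow both conditions:** remove cortisol and amylase from the third MANOVA and keep HRV and the SSSQ-G there. Report saliva as an exploratory time course with an order-group comparison, and make no condition claim.

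The cost is wording and a checklist line, with no extra samples. In the second case the salivary part of the abstract's expectation of higher stress responses under pain is given up, although no numbered hypothesis depends on it.

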### Explorative analyses

All outcomes for explorative analyses will be assessed at baseline in both study phases.

#### Fear avoidance.

Fear of movement/(re)injury due to physical activity will be measured with the German version of the Tampa Scale of Kinesiophobia (TSK) for the general population (TSK-G; [51,76]). The TSK-G is a modified version of the original TSK [77] for individuals with chronic pain. The questionnaire includes 17 items that are rated on a 4-point Likert scale from 1 = *strongly disagree* to 4 = *strongly agree*, with a higher total score representing higher FA. Psychometric property show acceptable internal consistency (*⍺* = .75; [76]).

#### Avoidance Endurance.

We will assess Avoidance and Endurance with the Avoidance-Endurance Questionnaire (AEQ; [52]) which focuses on pain-related behavioral, cognitive, and affective responses to pain. It consists of 49 items rated on a 7-point Likert scale ranging from 0 = *never* to 6 = *every time*. Psychometric properties show good internal consistency (*⍺* = .84; [52]).

#### Pain catastrophizing.

Pain catastrophizing will be assessed by the German version of the Pain Catastrophizing Scale (PCS; [78]). It consists of 13 Items rated on a 5-point Likert scale from 0 to 4, with a higher score indicating greater catastrophizing. The PCS is a broadly implemented questionnaire in the context of (CP)LBP (e.g., [30]) showing good internal consistency (*⍺* = .92).

#### Coping strategies for pain.

Coping with pain and pain-related distress will be assessed with the emotional pain processing questionnaire (FESV; German: Fragebogen zur Emotionalen Schmerz-verarbeitung; [54,55]). The FESV consists of 38 items and shows satisfactory reliability (*r*_*tt*_ = .78) and internal consistency (*⍺* = .77 - *⍺* = .83; [55]).

#### Chronic stress.

To assess how stressful participants perceive their life, we will employ the German version of the Perceived Stress Scale (PSS-10; [79]). Participants rate 10 items on a 5-point Likert scale from 0 to 4 with higher scores indicating higher perceived stress. The PSS-10 has been validated in a representative German community sample that revealed good internal consistency (*⍺* = .84) and construct validity [79].

### Data collection and management

When filling out the online screening-questionnaire, participants generate their personal study code, which follows them throughout the experiment. The questionnaire data are collected online and kept in accordance with the data protection guidelines of the European Union (EU-DGP). Until the pseudonymization allocation list is deleted, participants can ask for their data to be deleted at any time upon stating their assigned code. Data collected during the study are archived for 10 years before being deleted. Contact details will be maintained separately from questionnaire data. The collected data will be marked with the individual study codes to ensure pseudonymization. The list with codes will be kept separately and is password protected. All collected data will be stored in a secured research data storage system provided by the Friedrich-Alexander-Universität Erlangen-Nürnberg.

### Statistical methods

Qualitative analysis on feasibility and acceptability in phase 1 will be carried out with MAXQDA Analytics Pro [80]. Data of phase 2 will be analyzed using a repeated-measures design. Correlations of dependent variables will determine if multivariate analyses of variance (MANOVAs) or separate analyses of variance (ANOVAs) are indicated, following common recommendations of moderate intercorrelation [81].

The first MANOVA will include the within-subjects factor *condition* (PainSim + vs. PainSim-) and dependent variables measuring task-related fear of movement, pain intensity, impairment and emotional distress. A second MANOVA will assess *mobility* (LROM, LF, MV). And a third MANOVA will examine stress (HRV, salivary cortisol, salivary amylase, subjective stress) in the same manner. Psychophysiological data (e.g., HRV-data) that deviate (significantly) from the other data (i.e., outliers) will be excluded in accordance with the established practices in the literature. The pattern of missing data is tested with MCAR-test. If the missing data is missing completely at random, we will conduct multiple imputation.

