**Methods:**

To address this gap, 76 pain-free participants (20: phase 1; 56: phase 2) will perform standardized movement tasks (Back Performance Scale, Sit-To-Stand-Test) with and without wearing a back pain simulator in a within-subject design. Movement will be recorded with wearable sensor-based and novel radar-based motion capture technology. Additionally, psychophysiological stress parameters (e.g., salivary cortisol, heart rate variability), and self-reports on stress, pain, and FA will be assessed. This will be followed by a qualitative feasibility and acceptability interview in phase 1. In this phase, we will evaluate the feasibility and acceptability of a novel back pain simulator enabling a standardized simulation of low back pain, and the motion capture technology. Phase 2 will investigate the effects of pain induction on self-reported pain, back pain-related movement parameters, and stress responses. Associations of these factors with FA will be analyzed. We anticipate high feasibility and acceptability. We expect higher pain ratings, lower mobility, and higher stress responses in the pain condition compared to the control condition. We expect FA to moderate mobility and stress responses in the pain condition.

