### Sample size calculation and recruitment

We aim to examine 76 participants (phase 1: 20, phase 2: 56). The sample size for phase 1 follows recommendations for feasibility pilot studies, as the purpose of phase 1 is to test procedures for phase 2 [48,49].

Sample size calculations for phase 2 were based on a repeated measures design and calculated with G*Power. Based on similar study setups [27], we anticipate a medium effect size of approximately *d* = .40 [50] resulting in a total sample size of *N* = 51 (parameters: *d* = .40, alpha = .05, 1 – beta = .80). To compensate for dropouts and possible technical issues leading to missing data (especially motion capture data) we will recruit 10% additional participants, resulting in a total sample of *N* = 56.

Recruitment for both phases is carried out and monitored by the study team. Phase 1 is currently being conducted (from June 2025 until the anticipated completion at the end of November 2025), phase 2 is planned to begin in January 2026 and continue for eight months. Each participant will be offered a compensation of €20. Alternatively, participating students can receive course credits.

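### The outcome correlations choose the confirmatory test, the listed MANOVAs do not answer the outcome-specific hypotheses (3c is in none), and the 80% power is that of one paired contrast

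*Protocol article*

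**What the plan says.** The Introduction of the protocol article opens its list with "The following hypotheses will be tested". Eight directional statements follow (1, 2, 3a, 3b, 3c, 4a, 4b, 4c), and none is named primary. The fifth begins "3c) Observer ratings of performance of task execution are worse in the condition with the low back pain simulator (PainSim", that is, the condition with the simulator.

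Statistical methods lets the data pick the model: "Correlations of dependent variables will determine if multivariate analyses of variance (MANOVAs) or separate analyses of variance (ANOVAs) are indicated". The only criterion is "following common recommendations of moderate intercorrelation", with no cut-off. Three MANOVAs are listed. The first has "dependent variables measuring task-related fear of movement, pain intensity, impairment and emotional distress". The second has the three mobility features. The third has HRV, cortisol, amylase and subjective stress.

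Under Sample size calculation and recruitment, "we anticipate a medium effect size of approximately" d = .40 leads, with alpha .05 and power .80, to N = 51 for a repeated measures design. Ten per cent is added to reach 56.

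The Abstract says "We expect FA to moderate mobility and stress responses in the pain condition", and the Introduction repeats the moderation aim. Its exploratory paragraph then describes whether fear avoidance is associated with mobility, HRV, stress and pain.

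**The concern.** A confirmatory plan should let a reader say beforehand which test decides which hypothesis. Here that link is broken in four places.

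- The form of the test is settled only after outcome data have been seen.
- On the MANOVA route, several hypotheses share one non-directional omnibus test. The simulator is built to raise pain intensity, so the first MANOVA can be significant for that reason alone and say nothing on fear, impairment or distress.
- One stated hypothesis has no listed analysis.
- The stated power belongs to a test that is neither of the listed multivariate tests nor one of eight tests with any allowance for their number.

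At stake is whether a significant result can be read as support for a particular hypothesis, and whether 51 evaluable participants give the power a reader would assume.

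**Working it through.** **1. Hypotheses against models.**

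| Hypothesis | Outcome | Listed model |
|---|---|---|
| 1 | Pain intensity | MANOVA 1 |
| 2 | Fear of movement | MANOVA 1 |
| 3a | Motion impairment | MANOVA 1 |
| 4a | Emotional distress | MANOVA 1 |
| 3b | LROM, LF, MV | MANOVA 2 |
| 4b | Subjective stress | MANOVA 3 |
| 4c | HRV | MANOVA 3 |
| none | Cortisol, amylase | MANOVA 3 |
| 3c | Observer ratings | none |

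Only MANOVA 2 corresponds to a single hypothesis, and 3b does not say whether one feature or all three must be lower.

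**2. The plan's own figure.** Inputs from the sample size section: d = .40, alpha = .05, N = 51. Read d as the standardised within-person difference and use the paired t-test, which equals a repeated-measures ANOVA with one two-level factor. The noncentrality is d × √n = 0.40 × √51 = 2.857, with 50 degrees of freedom and a two-sided critical value of 2.009. Power is 0.7999 (0.8078 at n = 52). A one-sided test would need 41, and two independent groups 99 per arm, so neither fits. N = 51 is therefore the size for one two-sided paired contrast.

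**3. Power of the listed MANOVAs at n = 51.** With a two-level within-subject factor, the test is Hotelling's T² on the p differences: noncentral F with p and n − p degrees of freedom. With equal correlation r among the differences, the noncentrality is

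- all p variables moving by d: n·p·d² / [1 + (p − 1)r]. For p = 4, r = .5: 51 × 4 × 0.16 / 2.5 = 13.06.
- one variable moving: n·d²·[1 + (p − 2)r] / {(1 − r)[1 + (p − 1)r]}. For p = 4, r = .3: 8.16 × 1.6 / (0.7 × 1.9) = 9.82.

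The protocol gives no correlations. The range .3 to .7 is an assumption for what it calls moderate.

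| Power | r = .3 | r = .5 | r = .7 |
|---|---|---|---|
| p = 4, one moves | 66% | 80% | 95% |
| p = 4, all move | 90% | 80% | 69% |
| p = 3, one moves | 70% | 81% | 96% |
| p = 3, all move | 90% | 81% | 73% |

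The power of the omnibus test thus runs from about 66% to 96%, on either side of 80%.

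**4. Power if the hypotheses are tested one by one.** Suppose hypothesis 1 is passed at 5% and the other seven are tested with Holm. The first step uses 0.05 / 7 = 0.00714, critical value 2.805 on 50 degrees of freedom. At d = .40 and n = 51 the power is 52.5%. The effect that gives 80% is d = 0.513. If 3b required all three features at that level, simulated power at d = .40 is 14% (r = 0), 27% (r = .5) and 33% (r = .7).

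**5. Moderation.** Moderation by fear avoidance means that the condition effect changes with the fear-avoidance score, which is an interaction of condition and score. An association between the score and an outcome can exist with no such interaction.

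**The case against.** Much can be said for the plan.

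- The selection rule looks at correlations among outcomes, not at condition effects. A simulation with four null variables, n = 51, an assumed cut-off of mean |r| ≥ .3 and true r from .25 to .35 gave error rates, given the route taken, of 4.8% to 5.1% for MANOVA and 5.2% to 5.9% per ANOVA. That stands: the data-driven choice by itself does little to the error rate. The harm is that the two routes answer different questions.
- Separate ANOVAs do test single outcomes at a nominal 5%. That stands too, so the mismatch in pooling belongs to the MANOVA route.
- Follow-up tests and a multiplicity rule may sit in a document that is not shown. A reader might infer that uncorrected follow-up tests are planned, or that a 5% error rate over all eight hypotheses is promised and broken. The article says neither, and the point does not rest on it.
- A reader might infer that the MANOVAs are underpowered throughout. They are not. Power falls lowest with one moving, uncorrelated variable, and in that case the plan's own rule leads to ANOVAs.
- A reader might infer that the sample size is miscalculated. It is not: N = 51 reproduces, and "we will recruit 10% additional participants, resulting in a total sample of" 56 agrees with 51 × 1.10 = 56.1.
- Fear avoidance is exploratory, and an article may leave its model elsewhere. Even so, the announced aim and the described analysis differ within this article.

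**Conclusion.** The point holds, on stated text alone. The plan leaves the form of the test to the observed correlations. Its first and third MANOVAs pool directional hypotheses that they cannot separate, and the third adds two markers without a condition hypothesis. Hypothesis 3c has no listed model, and the moderation aim is matched only by an association.

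The 80% is correct for one two-sided paired contrast with 51 evaluable participants. It is not the power of the listed MANOVAs (about 66% to 96%), nor of eight hypotheses with any adjustment (about 52% for one single-variable hypothesis at the first Holm step over seven, given that hypothesis 1 is passed).

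These figures assume d = .40 for the within-person difference, normal differences, and equal correlations of .3 to .7 for the MANOVAs. The Holm figure for a single variable does not depend on the correlations.

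**What to change.** Before phase 2 outcome data are examined, amend Statistical methods and the sample size text as follows.

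1. Pre-specify one two-sided condition contrast per hypothesis on a named score, whatever the correlations, and include observer ratings for 3c.
2. Test hypothesis 1 first at 5% as the manipulation check. If it is passed, test the other seven (2, 3a, 3b, 3c, 4a, 4b, 4c) with Holm.
3. Name one deciding feature for 3b. Requiring all three would bring its power to about 14% to 33% at d = .40.
4. Report the MANOVAs as supportive and the salivary markers as exploratory.
5. Examine fear-avoidance moderation, as exploratory, by regressing the within-person condition difference on TSK-G.
6. Restate the power: 80% for one contrast at 5% with 51 evaluable participants. For a single-variable hypothesis at the first Holm step, given that hypothesis 1 is passed, state about 52% at d = .40, or 80% at d = .51.

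The cost is wording, an update of the registration and a less favourable stated power. No extra participants are needed.
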